### Secondary outcomes

#### Objective 2 (secondary objective (a))

Secondary outcomes for secondary objective (a) are evaluated at Baseline (Y0) through the qualitative assessment of patient questionnaires which are adherent to a theoretical framework for the acceptability of novel or self-sampling healthcare interventions [12, 13].

#### Objective 3 (secondary objective (b))

Secondary outcomes for secondary objective (b) are evaluated at all time points (Y0 – Y3) and will entail the assessment of true positive and false negative rates in this participant cohort to observe > 87% sensitivity. True positive (TP) cases are defined as the confirmation in the detection of colorectal neoplasia at time of colonoscopy for patients with preceding positive FIT results (≥6 μg/g f-Hb) and will be evaluated at thresholds of 6, 10 and 100 μg/g for patients meeting this criteria of TP.

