#### To evaluate the sensitivity of FIT for the detection of CRC in patients with lynch syndrome

The observation of true positive FIT results will be confirmed by the detection of CRC at the time of colonoscopy, and subsequent confirmation via pathology reports for patients with preceding positive FIT results (≥6 μg/g f-Hb).

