### Outcomes and endpoints

A detailed description of the objectives and the measurement of study outcomes is provided herein (see Table 3).

**Table 3 Tab3:** Measurement timepoints of study objectives

*Study Objectives*		*Measurement Timepoints*				
*Objective Type*	*Objective Summary*	*Baseline (Y0)*	*Y1*	*Y2*	*Y3*	*Passive Follow-Up (Y4-Y7)*
Objective 1 (Primary)	To evaluate the specificity of FIT for the detection of CRC and AA’s in patients with LS.	x	x	x	x	
Objective 2 (Secondary a)	To identify and explore acceptability, views, and preferences of FIT in this patient population	x				
Objective 3 (Secondary b)	To evaluate the sensitivity of FIT for the detection of CRC in patients with LS	x	x	x	x	
Objective 4 (Secondary c)	To evaluate the sensitivity of FIT for the detection of AA’s in patients with LS	x	x	x	x	
Objective 5 (Exploratory)	To examine and characterise the faecal microbiome of patients with LS.	x	x	x	x	
Objective 6 (Exploratory)	To observe the incidence of interval CRCs for LS patients with FIT negative results (< 6 μg/g f-Hb)					x^a^

^a^*This outcome will be measured in a subset of study participants*

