#### Objective 4 (secondary objective (c))

Secondary outcomes for secondary objective (c) are evaluated at all time points (Y0 – Y3) and will entail the assessment of true positive and false negative rates in this participant cohort to observe > 87% sensitivity. True positive cases in this context are defined as the confirmation in the detection of AA’s alone at time of colonoscopy for patients with preceding positive FIT results (≥6 μg/g f-Hb) and will be evaluated at thresholds of 6, 10 and 100 μg/g for patients meeting this criteria of TP.

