## Abbreviations

FIT: Faecal immunochemical test
CRC: Colorectal Cancer
CN: Colorectal Neoplasia
ACN: Advanced Colorectal Neoplasia
LS: Lynch Syndrome
SOC: Standard of Care
MMR: Mismatch Repair
EPCAM: Epithelial cell adhesion molecule
NHS: National Health Service
REC: Research Ethics Committee
HRA: Health Research Authority
SP: Study Participants
LoD: Limit of Detection
f-Hb: Faecal Haemoglobin
rRNA: Ribosomal Ribonucleic Acid
PI: Principal Investigator
CI: Chief Investigator
ISF: Investigative Site File
GCP: Good Clinical Practice
GDPR: General Data Protection Regulation
mITT: Modified Intention-To-Treat
CLIA: Clinical Laboratory Improvement Amendments
SAE: Serious Adverse Event

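### The outcome definition for CRC sensitivity counts colorectal neoplasia as a true positive, contradicting the CRC-only objective, and the >87% target cannot realistically be demonstrated

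*Protocol article*

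**What the plan says.** Three places in the protocol article describe the target of Objective 3.

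- Objectives section, CRC-sensitivity objective: "The observation of true positive FIT results will be confirmed by the detection of CRC at the time of colonoscopy", with confirmation by pathology report.
- Outcomes and endpoints, Table 3: "To evaluate the sensitivity of FIT for the detection of CRC in patients with LS".
- Secondary outcomes, Objective 3: "True positive (TP) cases are defined as the confirmation in the detection of colorectal neoplasia at time of colonoscopy", for patients with a preceding FIT of at least 6 μg/g, evaluated at 6, 10 and 100 μg/g.

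For comparison, Objective 4 is worded narrowly: "True positive cases in this context are defined as the confirmation in the detection of AA’s alone at time of colonoscopy". The Abbreviations list has the entry "CN: Colorectal Neoplasia" in addition to separate entries for CRC and for advanced colorectal neoplasia.

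On the target, Objective 3 plans "the assessment of true positive and false negative rates in this participant cohort to observe > 87% sensitivity". Objective 4 repeats the phrase "true positive and false negative rates in this participant cohort to observe" with the same 87% figure. Neither paragraph says what a false negative is, and neither gives a source for 87%. The sample-size text under Study design covers specificity only: 352 of 400 participants (88%) are expected to be free of advanced neoplasia.

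**The concern.** Sensitivity is a proportion among people who have one named disease, so numerator and denominator must refer to that disease. Here the objective names CRC and the outcome paragraph counts a wider category. The wider term is hard to dismiss as shorthand, because the article keeps the three terms apart in its abbreviations and restricts Objective 4 to AAs when it means only those.

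Two analysts could follow the article faithfully and report very different values under the label CRC sensitivity. AAs would also contribute to both secondary sensitivity objectives. Readers would then compare the result with an 87% target whose origin is not given and which the sample was not sized to test.

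**Working it through.** **1. The plan's own sizing.** Inputs from Study design: n = 352, null specificity 0.90, true specificity 0.94, one-sided 5% score test.

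Power = Φ[(√n(p1 − p0) − 1.645√(p0(1 − p0))) / √(p1(1 − p1))] = 86.0%, against 87% stated. The Wald 95% interval width is 2 × 1.96 × √(0.94 × 0.06/352) = 4.96%, against about 5% stated. Both reproduce. This 87% is power for specificity and has no bearing on the 87% sensitivity target. The same text implies 400 − 352 = 48 participants with CRC or AA combined; it does not split them.

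**2. What the definition does to the estimate.** Assumed illustration, chosen to add up to 48: 5 CRCs of which 4 are FIT-positive, and 43 AAs of which 17 are FIT-positive.

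| Reading | True positives | False negatives | Result |
|---|---|---|---|
| CRC only (Objectives section, Table 3) | 4 | 1 | 4/5 = 80% |
| Neoplasia as true positive, only missed CRC as false negative | 4 + 17 = 21 | 1 | 21/22 = 95% |
| All advanced neoplasia in both | 21 | 1 + 26 = 27 | 21/48 = 44% |

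The same data fall on either side of 87%. If the neoplasia term also covers non-advanced adenomas, which the article does not settle, the last two rows change again.

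**3. How many CRCs there might be.** The article gives no count, so this is a range from its own figures under stated assumptions.

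- Low end: the yield in the population screening pilot, 400 × 7.3/3933 = 0.7.
- High end: all 400 participants carry MLH1 variants, with a constant hazard from 46% risk over ages 25 to 70 and five years of accrual. −ln(1 − 0.46)/45 = 0.0137 per year; 400 × 0.0137 × 5 ≈ 27.
- The same calculation for an all-MSH2 cohort (35%) gives about 19.

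**4. What >87% means on such counts.**

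- As a point estimate: 6/7 = 85.7% fails and 7/8 = 87.5% passes, so with 7 or fewer CRCs the target is met only if none is missed.
- Exact 95% lower limit when all m CRCs are detected is 0.025^(1/m): 48% for 5, 59% for 7, 69% for 10, 83% for 20. It first exceeds 87% at m = 27.
- Rejecting 87% at one-sided 5% (a level borrowed from the specificity test) with all detected needs 0.87^m ≤ 0.05. 0.87^21 = 0.054 and 0.87^22 = 0.047, so at least 22 CRCs, with none missed.
- With exactly 22 CRCs and true sensitivity 95%, the chance of missing none is 0.95^22 = 32%. Even if all 48 expected advanced neoplasias were CRCs, 46 detections would be needed and power would be 57%.
- With 5 CRCs the point-estimate target is met with probability 0.87^5 = 50% if true sensitivity is 87%, and still 0.70^5 = 17% if it is 70%.

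**The case against.** The strongest reply is that the article already contains the right definition. The Objectives section asks for CRC confirmed by pathology, nothing says that the later paragraph overrides it, and a full protocol or analysis plan not shown here may use it. It is also fair that the article never defines colorectal neoplasia beyond expanding the abbreviation, so including small adenomas is a reading of ordinary usage. These points limit how much can be said about what will be done. They do not remove the conflict: two definitions of one outcome stand in one document.

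On the target, the article speaks only of observing more than 87%. It names no test, success rule or power for sensitivity, and it states no CRC count. That stands, and it is why the target can remain as a description.

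Several stronger readings are tempting but unsupported.

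- A reader might infer that the wording inflates CRC sensitivity. That holds only if false negatives stay CRC-only; a consistent neoplasia reading lowers the figure in the example.
- A reader might set the cited 82.2% sensitivity against 87%. That figure is at 20 μg/g, while the study cut-off is 6 μg/g, and for the same test and population a lower cut-off cannot reduce sensitivity.
- A reader might take the Discussion as predicting lower sensitivity in Lynch syndrome. It only raises the possibility.
- A reader might argue that 87% sensitivity for AAs is incompatible with the roughly 10% FIT positivity anticipated. That 10% concerns Years 1 and 3 and comes from early emergency-service data, whereas the 12% with advanced neoplasia is a sizing figure for CRC and AA combined.

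**Conclusion.** The Objective 3 outcome definition is wrong as written: it contradicts the Objectives section and Table 3, and with false negatives undefined the resulting figure is not CRC sensitivity. In the assumed example it could be reported as 95% or 44% where CRC sensitivity is 80%. The direction of the error cannot be determined from the document.

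The point about >87% is smaller. The target is underived, and the study cannot realistically demonstrate it: at least 22 CRCs with none missed are needed, and under the assumptions above only a cohort close to all MLH1 carriers would reach that count. It would go too far to call the target meaningless, since an observed proportion can still be described against it. This part rests on an assumed CRC count and a borrowed significance level. Objective 3 is secondary, and the primary specificity sizing is unaffected.

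**What to change.** In the Objective 3 outcome paragraph, replace the neoplasia term with pathology-confirmed CRC, and define a false negative as CRC with FIT below the threshold being evaluated. Keep AAs in Objective 4. If a combined CRC and AA sensitivity is wanted, report it as a separately named measure.

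In Objectives 3 and 4, present >87% as a descriptive benchmark, and report each sensitivity with its case counts and an exact 95% confidence interval.

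The cost is wording in two outcome paragraphs, handled through the amendment route that the article describes if it counts as a study change. No new data or participants are needed. The authors give up only the suggestion that the study can confirm a sensitivity above 87%.

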F-Hb results to come from this study will not be directly disclosed to participants. Site Principal Investigator’s (PI’s) will receive electronic reports of f-Hb results if ≥6 μg/g study participants’ directly from the Southern Hub laboratory via NHS secure and encrypted emails in Years 1 and 3 (the intervening years between a study participant’s SOC colonoscopy) to inform triage for colonoscopy. FIT positivity in study participants will be determined by the limit of quantification (LoQ) at the pre-determined threshold of ≥6 μg/g f-Hb [22].

Although it is anticipated that only a small minority of study participants may meet criteria for an additional interval colonoscopy at Years 1 & 3 (approximately 10%, based on early data as part of a preceding emergency clinical service evaluation), those that are identified as “FIT positive” at the specified study periods will be contacted by their respective local PI to discuss their FIT results and advised to proceed with a colonoscopy which will be triaged via the NHS’ urgent two-week-wait (2WW) referral pathway.

Throughout the duration of the study, endoscopy and pathology reports will be securely sent from respective study sites to the coordinating centre for the abstraction of relevant outcome data which will be stored and managed within the FIT for Lynch REDCap database.

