### Primary outcomes

#### Objective 1 (primary)

Primary outcomes are evaluated at all time points (Baseline (Y0) + Years 1-3 (Y1-Y3)) and will entail the assessment of true negative and false negative rates in this participant cohort to observe ≥90% specificity. In this context, true negative is defined as having no visible CRC or AA’s at time of colonoscopy and a subsequent normal or “negative” endoscopy and/or pathology report for participants with preceding FIT negative (< 6 μg/g f-Hb) results.

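### The wording for sensitivity at 10 and 100 μg/g leaves the denominator open, and two of its three readings overstate sensitivity; specificity is defined only at 6 μg/g

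*Protocol article*

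**What the plan says.** Objective 3 (CRC) opens with an "assessment of true positive and false negative rates in this participant cohort to observe > 87% sensitivity". It continues: "True positive (TP) cases are defined as the confirmation in the detection of colorectal neoplasia at time of colonoscopy for patients with preceding positive FIT". A positive test is given there as 6 μg/g or more. The true-positive cases "will be evaluated at thresholds of 6, 10 and 100" (in μg/g), and the population for this step is worded as follows: "for patients meeting this criteria of TP". Objective 4 repeats the rule and the target for advanced adenomas (AA).

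The section on FIT results reporting ties positivity to one value: "FIT positivity in study participants will be determined by the limit of quantification (LoQ) at the pre-determined threshold of ≥6 μg/g f-Hb". Objective 1 defines a true negative "for participants with preceding FIT negative (< 6 μg/g f-Hb) results", and the Objectives section of the article uses the same cut-off. Specificity at 10 or 100 μg/g is not mentioned.

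Under Baseline recruitment, f-Hb is to be reported as a concentration down to 1 μg/g. In Table 1, colonoscopy is standard of care at baseline and Year 2. At Years 1 and 3 a referral follows only if FIT is 6 μg/g or more. Objectives 3 and 4 are evaluated at all four time points.

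**The concern.** Sensitivity at a cut-off is the share of all confirmed lesions with FIT at or above that cut-off. A lesion below the cut-off is a false negative there, including one that was positive at a lower cut-off. Objectives 3 and 4 define a true positive at 6 μg/g only, do not define a false negative, and then limit the multi-threshold evaluation to patients who are already true positive at 6. An analyst following that clause would drop every lesion that FIT missed at 6.

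The figures at stake are the results at 10 and 100 μg/g for two secondary objectives and, on the literal reading, the result at 6 as well. The Discussion raises false positives and additional colonoscopies as limitations, and the preceding emergency service escalated patients at 10 μg/g. Sensitivity at a higher cut-off bears on those limitations only beside the specificity at the same cut-off.

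**Working it through.** **The plan's own figures.** The article gives no sample size or power for sensitivity at any cut-off. Its figures for specificity (n = 352, true value 94%, null 90%, one-sided 5% score test) reproduce:

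- 95% CI width = 2 × 1.96 × √(0.94 × 0.06/352) = 4.96%, against about 5% stated.
- Power = Φ[(0.04 − 1.645 × √(0.90 × 0.10/352)) / √(0.94 × 0.06/352)] = 86.0%, against 87% stated.

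Neither depends on the disputed clause.

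**Three readings.** Let Se(c) be the true sensitivity at cut-off c among all confirmed lesions. The cut-offs are nested: any lesion at or above 10 or 100 is also at or above 6.

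- A. Only patients true positive at 6 are evaluated: reported value = Se(c)/Se(6).
- B. True positives are recounted at c, but false negatives stay fixed at below 6: reported value = Se(c)/(Se(c) + 1 − Se(6)). Lesions between 6 and c are in neither group.
- C. All confirmed lesions stay in the denominator: reported value = Se(c).

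**Example.** Take Se(6) = 87%, the protocol's target value. Assume that 90% and 50% of those true positives reach 10 and 100 μg/g. These two shares are not in the documents. Then Se(10) = 0.87 × 0.90 = 78.3% and Se(100) = 0.87 × 0.50 = 43.5%.

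| Cut-off (μg/g) | A: TP at 6 only | B: FN fixed at below 6 | C: all lesions |
|---|---|---|---|
| 6 | 87/87 = 100% | 87/(87 + 13) = 87% | 87% |
| 10 | 78.3/87 = 90% | 78.3/(78.3 + 13) = 85.8% | 78.3% |
| 100 | 43.5/87 = 50% | 43.5/(43.5 + 13) = 77.0% | 43.5% |

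**Range.** Under A the factor is 1/Se(6): 1.05 at 95%, 1.15 at 87%, 1.25 at 80%, 1.43 at 70% and 2.00 at 50%. Under B, with the same assumed shares:

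- Se(6) = 70%: 63/93 = 67.7% against a true 63% at 10, and 35/65 = 53.8% against 35% at 100.
- Se(6) = 50%: 45/95 = 47.4% against 45% at 10, and 25/75 = 33.3% against 25% at 100.

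**In counts.** The plan expects 400 − 352 = 48 participants with advanced neoplasia. At 87%, 48 × 0.87 ≈ 42 would be FIT positive at 6, so about 6 would leave the denominator under A.

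**Time points.** Reading C needs lesions below the cut-off to be found. At baseline and Year 2 colonoscopy does not depend on that year's FIT result. At Years 1 and 3 it is triggered only at 6 μg/g or more, so lesions below 6 are largely unverified. Pooling all four years would overstate sensitivity at every cut-off even with the clause removed.

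**Specificity at the higher cut-offs.** With 352 lesion-free participants, the 95% half-width 1.96 × √(p(1 − p)/352) is about 2.0 points at an assumed 96% and about 1.0 point at an assumed 99%.

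**The case against.** The strongest reply is that no denominator for 10 or 100 μg/g is stated, and that the opening sentence of each objective names false negatives in the cohort. With positivity fixed at 6, those are the lesions that reading A would drop. The grammatical subject of the clause is true-positive cases, that is, the numerator. Because the cut-offs are nested, limiting the numerator to true positives at 6 loses no case and causes no bias. Reading A would also make the 87% target at 6 meaningless.

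This stands as far as it goes: inflation is not certain, and reading C may be intended. It does not clear the text. If the clause limited only the numerator it would be redundant. Naming false negatives is not enough unless they are redefined at each cut-off, as reading B shows. Objective 1 describes its specificity assessment in terms of true negatives and false negatives, which are not the components of specificity, so a correct unstated denominator cannot be presumed.

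A reader might infer three stronger points that the documents do not support:

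- That the trial will report inflated sensitivity. The wording permits this but does not settle it.
- That an inflated 90% at 10 μg/g would wrongly meet the target. The target above 87% is not stated to apply at 10 or 100.
- That the study means to choose a cut-off and has omitted half of that analysis. Cut-off selection is not among the objectives, 6 μg/g is fixed in advance, and specificity at 10 and 100 may be left to a fuller protocol or SAP that is not shown.

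**Conclusion.** The point holds as a defect in a stated rule for two secondary objectives. The clause allows three readings, and only the one that keeps every confirmed lesion in the denominator gives sensitivity at 10 and 100 μg/g. The literal reading overstates it by 1/Se(6), which is 1.15 at the 87% target and more if FIT performs less well. Holding false negatives at below 6 also overstates it, by an amount that grows with the share of lesions between 6 and the higher cut-off (77% against 43.5% at 100 in the example). These sizes rest on the target value for Se(6) and on assumed shares above 10 and 100.

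Naming the higher cut-offs for sensitivity alone is the lesser part. It makes the evaluation one-sided as written but is not in itself an error. The primary objective and its power are unaffected.

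**What to change.** In Objectives 3 and 4:

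- Delete the clause that limits the evaluation to patients already meeting the true-positive definition.
- State that at each of 6, 10 and 100 μg/g, sensitivity is the proportion with FIT at or above that cut-off among all participants with the confirmed target lesion and a paired FIT, and that lesions below that cut-off count as false negatives.
- Base these estimates on baseline and Year 2. Report Years 1 and 3 separately, with a note that lesions below 6 μg/g are largely unverified then.

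In Objective 1, keep 6 μg/g as the primary analysis cut-off. Add specificity at 10 and 100 μg/g as secondary, among participants without CRC or AA, beside the matching sensitivity.

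The f-Hb concentration is already recorded for every returned kit, so the cost is a wording change and a few extra table rows, with no new data and no change to the sample size.

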#### Objective 4 (secondary objective (c))

Secondary outcomes for secondary objective (c) are evaluated at all time points (Y0 – Y3) and will entail the assessment of true positive and false negative rates in this participant cohort to observe > 87% sensitivity. True positive cases in this context are defined as the confirmation in the detection of AA’s alone at time of colonoscopy for patients with preceding positive FIT results (≥6 μg/g f-Hb) and will be evaluated at thresholds of 6, 10 and 100 μg/g for patients meeting this criteria of TP.

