### Rationale for current study

Presently, FIT is used as a non-invasive triage tool for referring people for colonoscopic (or other) investigation in asymptomatic patients invited to participate in national bowel cancer screening programmes, as well as in symptomatic patients presenting to primary care with symptoms suggestive of CRC who require urgent colonoscopy [9, 10]. The utility of FIT for the purpose of surveillance in patients with Lynch Syndrome, however, has not previously been formally assessed to our knowledge.

During the COVID-19 pandemic, an emergency national clinical service utilising FIT was implemented by our team for people with LS within England, entitled “*Rapid evaluation of Faecal immunochemical testing (FIT) levels in individuals with a Lynch Syndrome pathogenic variant to determine a revised threshold for colonoscopy in response to the COVID-19 pandemic* (Short Title: “Rapid FIT for Lynch”) [11]. Data from this emergency service has provided important preliminary insights into the design of the research study described in this paper. In this response to the COVID-19 pandemic, eligible LS patients were mailed a FIT kit in lieu of their standard surveillance colonoscopy, which may have been cancelled or indefinitely postponed, as a way of escalating priority of suspected high-risk patients (as defined by having a FIT result ≥10 μg of haemoglobin (Hb) per gram of faeces (f-Hb)).

Overall, an uptake rate of 63.7% was observed (375/588) for those LS patients who had returned their FIT kit to the laboratory for analysis. We also observed earlier diagnoses of CRC in patients whose investigations were escalated after a positive FIT.

Given the acceptable uptake rate of FIT in this LS patient cohort, we believe that a structured programme enabled by longitudinal research with annual FIT alongside biannual colonoscopy is warranted to sufficiently examine the efficacy of FIT as an additive, non-invasive diagnostic modality for the purposes of surveillance in patients with Lynch Syndrome.

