Assuming approximately three quarters of the eligible 2745 LS patients are due for colonoscopy within the 18 month recruitment period (2745 × 0.75 = 2059), and in considering the projected response/uptake rate of ~ 63%, (which has since been observed in the same patient population as part of the continuing NHS England clinical service evaluation [18]), it is estimated that 1297 individuals will return a FIT sampling kit.

On aiming to recruit 400 Lynch Syndrome patients on surveillance (when considering existing available funding), we anticipate 352 (88%), will not have detectable advanced neoplasia and will be used to evaluate the specificity. Assuming true specificity of 94%, then the width of a 95% confidence interval will be approximately 5%. These numbers would also provide 87% power to show that the specificity is at least 90%. This is based on a one-sided one-sample score test of proportions with a 5% significance level using STATA/SE v. 17.0.

We will employ a modified intention-to-treat (mITT) approach whereby participants who return at least 1 FIT kit and have an outcome from colonoscopy are available for analysis. Participants whose colonoscopy result is unavailable are likely to be relatively uncommon when considering the high rate of colonoscopy surveillance adherence in this patient population [19, 20]. Nonetheless, we will report the frequency of those without colonoscopy and the frequencies of those returning 0, 1 or 2 FIT kits.

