## Discussion

As the implementation of our emergency national clinical service evaluation has elucidated thus far, the utility of FIT may present clinical value for patients with Lynch Syndrome as a means of non-invasive CRC surveillance in intervening years between colonoscopy, and as an efficient mechanism in risk-stratifying the highest risk patients within this patient population [18]. Though qualitative analysis is presently underway in understanding LS patient attitudes and perceptions towards this diagnostic device, the patient response rate (63%) exemplified a favourable response overall. Provided the short duration of this clinical service as an emergency measure to the COVID-19 pandemic, further investigation on the efficacy of this novel intervention is warranted and may be enabled by this longitudinal, multi-centre, prospective research study.

In addition to elucidating overall efficacy of FIT in patients with Lynch Syndrome, we aim to characterise the faecal microbiome of individuals with Lynch Syndrome (as outlined in Objective 4) through residual faecal DNA. The data to be collected from this study may facilitate deeper insights into the unique bacterial communities which reside in the microbiome of LS patients which may have important clinical implications. Moreover, we envisage subsequent versions of this protocol may allow for the assessment of cancer-associated genetic changes in human DNA from stool which have the potential to improve the accuracy of a microbiome-based test.

At the time of this writing, eleven NHS Trusts throughout England and Scotland have been included as study sites and active recruitment is underway. Nonetheless, we recognise that this study may present certain limitations or issues, such as the potential for additional colonoscopies during intervening years between biennial surveillance colonoscopies, which may be considered invasive and potentially cause harm to no benefit to the patient.

Considering the unique histopathology and morphology of LS-associated neoplasia (with a higher frequency of flat/subtle neoplasia) [25], the sensitivity of FIT may be lower in comparison to the FIT sensitivity rates depicted within population-based screening programmes. The rate of false positives findings may also be slightly elevated when considering for example the prevalence of anastomotic inflammation from previous CRC resection in this patient population.

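### The >87% sensitivity target for advanced adenomas has no stated source and does not fit the plan's own prevalence, specificity and positivity figures at a surveillance round

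*Protocol article*

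**What the plan says.** All references are to the protocol article.

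- **Secondary outcomes, Objective 4.** The outcome "will entail the assessment of true positive and false negative rates in this participant cohort to observe > 87% sensitivity". It is restricted to adenomas: "True positive cases in this context are defined as the confirmation in the detection of AA’s alone at time of colonoscopy", after a FIT result of at least 6 μg/g. Objective 3 (CRC) carries the same >87%. Neither figure has a source or derivation.
- **Study design.** Of 400 recruits, "we anticipate 352 (88%), will not have detectable advanced neoplasia and will be used to evaluate the specificity". The remaining 48 (12%) have advanced neoplasia, with AA and CRC not separated. Specificity is assumed to be 94%. The one sensitivity cited is 82.2%, for CRC at 20 μg/g.
- **FIT kit results reporting and urgent colonoscopy triage.** The share expected to be FIT positive at Years 1 and 3 is "approximately 10%, based on early data as part of a preceding emergency clinical service evaluation".
- **Rationale for current study.** That service posted kits to Lynch patients in place of a due surveillance colonoscopy. It escalated high-risk patients, "as defined by having a FIT result ≥10 μg of haemoglobin (Hb) per gram of faeces".
- **Table 1.** At Years 1 and 3, colonoscopy follows only a FIT result of at least 6 μg/g. At baseline and Year 2 it is standard of care.
- **Discussion.** Because Lynch lesions are more often flat or subtle, "the sensitivity of FIT may be lower in comparison to the FIT sensitivity rates depicted within population-based screening programmes".

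**The concern.** Prevalence, specificity, sensitivity and overall positivity are tied by one identity, so fixing three of them determines the fourth. The plan gives a number for each, in different sections, and never puts them together. For a round in which 12% have advanced neoplasia, they do not agree.

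Two things are at stake. First, AA results will be read against a benchmark that the plan does not derive and that its own planning figures do not support, so a result in line with those figures would look like a shortfall. Second, if the benchmark is nearer the truth, expected positivity at the study cut-off is too low. AA also shares its target with cancer, although the plan offers no AA sensitivity from any source.

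**Working it through.** **1. The plan's own calculation reproduces.** Inputs: n = 352, null specificity 90%, true specificity 94%, one-sided 5% score test.

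- Power = Φ[(0.94 − 0.90 − 1.645 × √(0.90 × 0.10 / 352)) / √(0.94 × 0.06 / 352)] = Φ[(0.0400 − 0.0263) / 0.01266] = 86.0%, against 87% stated.
- Confidence interval width = 2 × 1.96 × 0.01266 = 4.96 points, against about 5.
- Specificity = 3684 / 3925 = 93.9%, against 94%.

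That 87% is power for specificity. It is no derivation of the 87% sensitivity target, and no such derivation is given elsewhere.

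**2. The identity.** Positivity = prevalence × sensitivity + (1 − prevalence) × (1 − specificity).

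**3. Positivity needed for 87%.** With 12% prevalence and 94% specificity: 0.12 × 0.87 + 0.88 × 0.06 = 0.1044 + 0.0528 = 15.7%, or 63 per 400. At 10%, the number is 40 per 400.

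**4. Sensitivity implied by 10% positivity in that round.** (0.10 − 0.0528) / 0.12 = 39.3% for AA and CRC combined. In counts: 40 positives, 21.1 of them false, leaving 18.9 true positives among 48.

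**5. AA alone.** The plan gives no AA prevalence, so I assume CRC is 0% to 2% of participants. True positives are 4.72% of participants.

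| CRC | AA | AA sensitivity if every true positive is AA | AA sensitivity if CRC is detected at 87% |
|---|---|---|---|
| 0% | 12% | 4.72/12 = 39% | 39% |
| 1% | 11% | 4.72/11 = 43% | (4.72 − 0.87)/11 = 35% |
| 2% | 10% | 4.72/10 = 47% | (4.72 − 1.74)/10 = 30% |

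**6. Prevalence at which 10%, 94% and 87% agree.** (0.10 − 0.06) / (0.87 − 0.06) = 4.9%, about 20 of 400. At 10% positivity and 94% specificity, combined sensitivity is 46% at a prevalence of 10%, 56% at 8% and 73% at 6%.

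**7. If positivity at ≥6 μg/g exceeds 10%.** With 12% prevalence and 94% specificity, combined sensitivity is 56% at 12% positivity and 81% at 15%.

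**8. Effect of pooling all four rounds.** Years 1 and 3 verify only FIT positives, so missed lesions there are not counted. As an illustration, let the rates in step 4 hold in every round. Observed sensitivity is then (4 × 4.72) / (2 × 12 + 2 × 4.72) = 18.88 / 33.44 = 56%, when the true value is 39%.

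**The case against.** The strongest reply is that the figures are not stated for the same round. The 10% is given for Years 1 and 3, after a recent colonoscopy, and the 12% has no stated time frame. At 5% prevalence in an interval year, 0.05 × 0.87 + 0.95 × 0.06 = 10.05%, and everything agrees. If the 12% were spread over two surveillance rounds at 6% each, positivity would be 0.06 × 0.87 + 0.94 × 0.06 = 10.9%, still roughly 10%. This stands as a limit on the point: the documents do not prove a contradiction. It does not settle the matter, because the plan states no such prevalence for any round and the source of the 10% tested people who were due surveillance, as participants are at baseline. Carrying the 10% to baseline is reasonable, but it is an inference.

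The 10% may also have been read at the service's ≥10 μg/g cut-off. Positivity at ≥6 μg/g would then be higher and the gap smaller. That is a reason to state the cut-off.

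Some stronger readings are tempting and are not supported:

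- **That AA sensitivity cannot exceed 83%.** The ratio 10/12 bounds AA and CRC combined. With 1% CRC, the strict AA maximum would be 10/11 = 91%.
- **That the CRC target conflicts too.** If CRC is about 1% of participants, 87% sensitivity adds about 0.9 points of positivity and contradicts nothing.
- **That Objective 4 is bound to fail.** It is a secondary objective with no test, power or success rule, and pooling with Years 1 and 3 would push the observed figure up.
- **That at most 48 cases will be available.** The objective covers Y0 to Y3, and later rounds may add cases.

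**Conclusion.** The point holds in conditional form. The >87% target for AA is underived, equals the CRC target despite the plan's own caution, and does not fit 12% prevalence, 94% specificity and 10% positivity taken at one surveillance round. Those figures imply about 39% for combined advanced neoplasia and about 30% to 47% for AA alone, against 87%.

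This rests on three assumptions: that the 10% applies at a round with 12% prevalence, that it applies at ≥6 μg/g, and that CRC is 0% to 2% of participants. The AA and CRC split does not change the conclusion within that range. A prevalence near 4.9%, or positivity near 15.7%, would remove the conflict.

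**What to change.** 1. In the Objective 4 outcome, drop >87% as the criterion for AA, or justify it with a source specific to AA and separate from CRC.
2. Report AA sensitivity as an estimate with a Wilson or exact 95% confidence interval. Base it on baseline and Year 2, where FIT-negative participants also have colonoscopy. Report AA found at Years 1 and 3 separately and amend Table 3 to match. To show the precision to expect, 19 of 48 in one round would give a Wilson interval of 27% to 54%.
3. Reconcile the planning figures in Study design, the triage section and Objective 4: state expected positivity at ≥6 μg/g and expected AA prevalence for each round, and say at which cut-off the 10% was observed.

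This is a change of wording only, with no effect on sample size or data collection. The cost is that the stated AA target, and possibly the expected positivity, become less favourable, and that cases found in Years 1 and 3 leave the sensitivity estimate.
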